## Abstract

Forest bathing practices benefit individuals’ physical and mental health. A growing number of published studies provide evidence of such effects in diverse populations and contexts. However, no literature has been found that evaluates the effects of forest bathing on people with intellectual disabilities. In this paper, we present a quasi-experimental pre–post protocol for assessing the preliminary efficacy and feasibility of a forest bathing intervention in a group of adults with intellectual disability. An 11-weekly session program will be applied in the forests of the Ollo Valley, Navarre (Spain). The preliminary efficacy outcomes will be blood pressure, psycho-physiological coherence parameters and quality of life. The feasibility of the intervention will be assessed through data on barriers and facilitators of the implementation process and indicators of environmental comfort (physiological equivalent temperature and thermic perception). This study offers an opportunity for people with intellectual disabilities to benefit from a forest bathing intervention and explore its effects not only on their quality of life, but also on the improvement in their physiological and psychological state. This feasibility study is an essential step to explore crucial aspects for a future full-scale trial.

## 1. Introduction

Currently, 55% of the people worldwide live in urban rather than rural areas, with this number projected to reach 68% by 2050 [1]. This tendency increases the necessity for people to utilize forest and green spaces for health and well-being purposes [2], underlying the value of nature. The positive effects of forest ecosystems on human health have been proven by numerous investigations across diverse disciplinary fields [3,4,5,6]. Shinrin-yoku or forest bathing has become a global trend during the past decade as a reaction to the current flood of stimuli from and the hectic daily life in our modern society [2]. It refers to the practice of immersing oneself in natural forest environments by mindfully using one’s senses [7,8].

Accumulated evidence confirms that forest bathing has quantifiable positive outcomes for individuals’ physical and mental health [9,10,11,12,13]. The physiological health benefits include increases in the parasympathetic activity, which plays an important role in physical recovery [14]; the decrease of physiological biomarkers, such as cortisol levels and alpha-amylase; [15] and the lowering of heart rate and blood pressure [16,17]. In addition, forest bathing mitigates respiratory problems [6,18], sleep disorders [19], depression [20], and high levels of blood glucose [11]. Moreover, these practices have positive effects on the immune system and some inflammatory parameters [8,12] There is also a positive impact on psychological and mental health from reducing stress, symptoms of depression and anxiety, negative emotions, confusion, and fatigue [6,8,14,21]. In addition, forest bathing increases the feelings of awe, gratitude, and selflessness, while improving mental relaxation and increasing attentional focus [8,14,21].

The studies cited above cover a wide range of populations, including both healthy people and those with pre-existing conditions. Special attention has been paid to people suffering from chronic cardiovascular and respiratory diseases, diabetes, skin diseases, and a weakened immune system [2,11], and also to mental health problems such as depression or psychotic disorders [22,23]. However, we found no studies addressing adults with intellectual disabilities. Intellectual disability is a term used when there are limits to a person’s ability to learn at an expected level and function in daily life [24]. These individuals frequently experience health disparities, such as the failure to be included in public health efforts and other prevention activities. A sign of this might be the aforementioned gaps in the literature that reveal a lack of intervention trials [25], specifically in the realm of forest bathing. 

In the Spanish context, forest bathing investigations are recent and still scarce. Some examples are exploratory studies focused on patients with fibromyalgia [26], from the general healthy public [27], and after the COVID-19 lockdown [28,29]. Therefore, the main goal of this study is to provide information about the health effects of forest bathing in adults with intellectual disabilities. It also aims to provide insights for future research involving this target group.

## 2. Study Design

A quasi-experimental, pre–post design will be carried out following the methodological framework for complex interventions proposed by the Medical Research Council [30]. This framework is a very helpful guide to identifying the key questions about complex interventions, and to designing and conducting research with a diversity of perspectives and appropriate choice of methods. Complex intervention research can be considered in terms of phases, although they are not necessarily sequential: (1) development or identification of an intervention, (2) assessment of the feasibility of the intervention and evaluation design, (3) evaluation of the intervention, and (4) impact of its implementation. Therefore, this study corresponds with the assessment of feasibility phase of the intervention in order to make decisions about progression to the next stage of evaluation.

This study is registered at ClinicalTrials.gov (accessed on 26 July 2022) (identifier: NCT05472571).

### 2.1. Objectives

Specifically, this study aims to:Estimate the preliminary efficacy of an 11-session forest bathing intervention on adults with intellectual disability.Examine the feasibility (facilitators, barriers, unforeseen events, and indicators of environmental comfort) of applying the intervention to adults with intellectual disability.

### 2.2. Sample Size Determination

Conventional sample size calculation does not apply due to the exploratory nature of the investigation at this stage of the MRC framework, whose main objective is to explore the preliminary efficacy and feasibility aspects of the implementation process [31]. Nevertheless, we considered that a minimum of 30 would be sufficient to give a reasonable indication of the likely effect size in line with other similar papers [32,33,34]. Assuming attrition of 15%, the study seeks to recruit 35 persons (the number of eligible participants with intellectual disabilities enrolled in the occupational center where the study will be carried out).

### 2.3. Participants and Recruitment

The study will be conducted in a social cooperative that manages an occupational center and supervised apartments for 35 adults (aged 18–36) with low-to-moderate intellectual disability (and in some cases diagnosed with dual disability) in the Ollo valley (Navarra, Northern Spain) (see Figure 1A). Adults only enroll in this center after getting an official diagnosis by a team of doctors, psychologists and social workers from the regional Health System and Social Security System. The diagnostic criteria are those established in the national law [35]. Only adults from this occupational center will be eligible for this study. 

The eligibility criteria for participants are the following:Inclusion criteria: (1) adults with intellectual disability who are already enrolled in the activities of the participant occupational center; (2) able to read and/or speak in Spanish; and (3) with their own or legal guardian’s informed consent.Exclusion criteria: (1) adults with intellectual disability from other associated centers who are not enrolled in the daily activities of the participant occupational center; (2) adults with intellectual disabilities who may require intense and individual supervision from their educators throughout the activity.

Literacy or numeracy will not be required aspects for participants’ inclusion. To ensure their understanding of any information provided, reference educators will assist participants during the information process and data collection moments, to support those who face difficulties understanding written documents (information letter, consent form, or questionnaires). A person’s reference educator is that caregiver who usually works closely with him/her and acts as his/her mentor in the center. 

One month before starting the recruitment, there will be an informative meeting between the university’s project leaders and all workers (manager, educators, and technicians) and users from the social cooperative. Participants and their educators will have the opportunity to ask questions and concerns about the intervention to the researchers, the cooperative manager, and center’s workers. Once they express their willingness to participate, the center’s social worker and psychologist will conduct a preliminary screening to ensure the participants fulfill the inclusion criteria. Eligible participants will receive an invitation letter together with written information about the project and the informed consent document. Researchers’ contact information will be also provided to clarify any issues that might arise.

Besides the collaboration between the social cooperative and the university, an association of forest owners (Foresna-Zurgaia) and an environmental consultancy (Basartea) are also included in the partnership. They will be mainly responsible for mapping and conditioning the forest pathways to conduct the intervention.

## 3. Data Collection Plan

Once participants sign the consent, the baseline measurement will take place before the first forest bathing session (two weeks before the intervention). The same set of measures will be collected right after finishing the last session (posttest) and seven months after completing the intervention (follow-up) (Figure 2). The timelapse before the follow-up data collection responds to a study recommendation of gathering mid- and long-term measures after a forest bathing-based intervention [36,37]. Since this is an exploratory study, we will take just the mid-term follow-up measures, as we understand that the long-term ones correspond to a full study. Although the general duration recommendation for mid-term is 6 months after finishing the intervention [32], we will consider 1 month of grace period before or after the 6 months target assessment time to take into account significant events in context. 

Two researchers will collect the physiological and psychological data in one allocated room in the occupational center. This room will be a big open area with windows overlooking the forest and furnished with coaches, exercise mats, tables, chairs, office, and craft supplies. This room will be familiar to participants, as they will perform different daily activities and meetings there. The three data collection events will take place in the same room.

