### 3.1. Outcomes, Measures and Instruments

First, sociodemographic variables will be collected, such as age, sex, disability grade, medication intake, mental comorbidities, geographical origin, and leisure time in contact with nature. Participants will fill out this data before starting the intervention. Then, preliminary efficacy outcomes will be estimated by psycho-physiological coherence (HRV parameters), blood pressure, and self-perceived quality of life measures.

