## 4. Detailed Procedure

### 4.1. The Forest Bathing Intervention

The forest bathing intervention follows the method developed by Forest Therapy Hub [46] from the base approach proposed by [name] and [name] [47,48]. It consists of 11 consecutive sessions (one session per week), each one lasting about 2 h (Figure 2). Each session involves an easy walk through a forest area, interspersed with non-intrusive activities of contact with the surrounding nature aimed at fostering mindfulness and the use of the five senses. Three routes have been designed and prepared for their use with this population: two of them in oak forests and a third one next to a river (Figure 1B). To adapt the process to participants’ characteristics and needs, the sessions have been designed cooperatively by the center’s education team, technicians, psychologist and social worker, and the main researchers of this project. Therefore, the process of forest bathing is agreed upon by the whole team and customized in terms of time, routes, physical demand, and reflective questions during the activities. For example, the guides will help the participants through reflective activities to identify and share their thoughts, as this is usually a challenging process for many of them. Also, the team selected routes with very gentle or no slope and will prepare the path to minimize any possibility of stumbling or slipping while walking.

Sessions will be carried out in groups of 6 to 9 participants and guided by a trained guide (see training description and guides characteristics in Section 4.2). Although participants will experience different activities each week (Figure 1C), sessions will always follow the same sequence of four parts (Figure 2). The first phase introduces the activity, the setting, and the participants. Secondly, the “initial phase” focuses on disconnecting from every thought that is not the present moment. Thirdly, the “intermediate phase” is centered on connecting to the environment. Lastly, the “final phase” aims to integrate all the experiences of the previous phases. In all the phases, participants are invited to share their impressions with the rest of the group.

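### Read literally, the posttest directly follows a forest session while baseline and follow-up do not, so the baseline-posttest change cannot separate the after-effect of session 11 from the programme effect

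*Protocol article*

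**What the plan says.** Section 3 (Data Collection Plan) fixes three assessments:

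- **Baseline:** "the baseline measurement will take place before the first forest bathing session (two weeks before the intervention".
- **Posttest and follow-up:** "The same set of measures will be collected right after finishing the last session (posttest) and seven months after completing the intervention (follow-up".

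On the programme, section 4.1 says: "It consists of 11 consecutive sessions (one session per week), each one lasting about 2 h". It adds: "Each session involves an easy walk through a forest area", with mindfulness and sensory activities along the way.

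Section 3.1 lists what is measured: "preliminary efficacy outcomes will be estimated by psycho-physiological coherence (HRV parameters), blood pressure, and self-perceived quality of life measures". Sections 3.1.1 and 3.1.2 have blood pressure and HRV taken seated and at rest, and section 3 uses one room for all three events. Section 2.1 makes the preliminary efficacy of the whole 11-session programme the first objective. The article text shown sets no interval between the end of the last walk and the posttest. Figure 2, which holds the schedule, is not shown.

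**The concern.** One of the three assessments comes straight after an exposure that is meant to move the outcomes; the other two do not. The Introduction counts "the lowering of heart rate and blood pressure" among the effects of forest bathing, and the Discussion itself separates the more lasting effect of repeated stays from that of isolated visits. The schedule as written cannot make that separation.

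Two readings are at stake. A change from baseline to posttest could be credited to the programme when it is partly or wholly the after-effect of one walk. A change from posttest to follow-up could be read as a fading benefit when it is only the absence of that same-day effect. Section 2.2 wants the sample to indicate the likely effect size and section 2 says the study informs progression to the next stage, so a mixed estimate would be carried into that decision.

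**Working it through.** **1. The assessments side by side**

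| Assessment | Timing (section 3) | Session just before? | Posture and place |
|---|---|---|---|
| Baseline | two weeks before the programme | no | seated rest, same room |
| Posttest | directly after session 11 | yes, about 2 h | seated rest, same room |
| Follow-up | seven months after the programme | no | seated rest, same room |

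Posture and place are common to all three. Recent exposure to a session is not.

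**2. What each contrast estimates**

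Let m be the mean without intervention, θ1 the programme effect at its end, θ2 the programme effect at seven months, and a the short-lived after-effect of session 11 (forest exposure, recent walking, or both; either sign). Ignore time trends, which no single-arm study can separate. The expected means are:

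- baseline = m
- posttest = m + θ1 + a
- follow-up = m + θ2

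Hence:

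- posttest − baseline = θ1 + a
- follow-up − posttest = θ2 − θ1 − a
- follow-up − baseline = θ2

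Three means cannot determine four unknowns, and θ1 and a appear only as a sum. The first two contrasts are affected. The third is not, but it measures persistence rather than the effect at the end of the programme. The planned test across time (section 6) includes the posttest, so it is affected too.

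**3. Size, as an illustration only**

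Inputs:

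- n = 30, the minimum in section 2.2. The recruitment target of 35 with 15% attrition leaves 35 × 0.85 = 29.75, so about 30.
- Two-sided 5%, the level in section 6.
- θ1 = 0, assumed, to isolate the effect of a.
- d = a divided by the SD of the paired change. The documents give no value, so a range is assumed.

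Formula: the paired t statistic follows a noncentral t distribution with n − 1 = 29 degrees of freedom and noncentrality d√n. The probability of a significant result is P(|T| > t crit), with t crit the 97.5% point of t on 29 degrees of freedom.

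| Assumed d | d√30 | Probability of significance, n = 30 |
|---|---|---|
| 0.2 | 1.10 | 18.5% |
| 0.3 | 1.64 | 35.5% |
| 0.5 | 2.74 | 75.4% |

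With all 35 completing, the figures are 21.0%, 40.7% and 82.0%. With a = 0 the probability would be 5%.

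This treats the baseline-posttest contrast alone. Section 6 plans an ANOVA or Friedman test across the time points, so the percentages are not the operating characteristics of the planned test.

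**The case against.** **The wording may only label a time point.** The sentence counts in weeks and months, and the posttest phrase may simply mean the end of the programme. Figure 2 or the full protocol may name a later day. Testing about 35 people within minutes of a walk, with two researchers and sessions in groups of 6 to 9, also looks hard to do. This stands as a reason to reconcile text and figure. It does not remove the point, because the text as written puts the posttest straight after the session.

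**All three assessments are resting measurements.** This is correct. A reader might infer that only baseline and follow-up are taken at rest; sections 3.1.1 and 3.1.2 say otherwise. What remains is carry-over beyond seated rest, since no minimum time since the walk is set.

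**Quality of life is unlikely to move with one walk.** This largely stands. The items are rated from never to always and concern personal outcomes, and nothing in the article suggests that a single session shifts them. The point is chiefly about blood pressure and HRV.

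**Unequal delays between participants are not documented.** This stands. No testing order or delay is given, and the point does not need it.

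**The study is exploratory and already concedes weak causal inference.** This lowers the stakes but does not answer the point. The Limitations name sample size and the lack of a control group, not the timing. Unlike the missing control group, the timing mismatch can be removed within the single-arm design.

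**Conclusion.** The concern holds in a limited form. If section 3 is followed literally, the baseline-posttest and posttest-follow-up contrasts for blood pressure and HRV combine the programme effect with any after-effect of session 11, and no planned measurement separates the two. Baseline versus follow-up is free of this.

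The size is unknown. Under assumed acute shifts of 0.2 to 0.5 SD and no programme effect, a significant baseline-posttest change would arise with probability about 18% to 75% at n = 30. These figures show what follows from the assumption, not a demonstrated bias.

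A reader might infer that the schedule builds in a false benefit. The documents do not support that: they give no acute effect size, the Introduction does not say whether the blood pressure effect is acute or lasting, and recent walking could push the readings either way. The after-effect could therefore exaggerate or mask a programme effect. Nor does the point undermine the feasibility objective.

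**What to change.** Schedule the posttest on a day without a session, within about a week of session 11, under the same conditions as baseline and follow-up. State that day in section 3 and make sure that Figure 2 agrees. If Figure 2 already shows a later day, correcting the wording of section 3 is enough.

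If the posttest must stay on the session day, describe the baseline-posttest change as a combined acute and programme effect, do not read the posttest-follow-up change as loss of programme benefit, and add the timing to the Limitations.

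The cost is one rescheduled measurement day, in a centre whose daily activities the participants already attend, and a posttest a few days later. The delay assumes that an after-effect of one walk has gone by then while an end-of-programme effect has not.

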### 3.1. Outcomes, Measures and Instruments

First, sociodemographic variables will be collected, such as age, sex, disability grade, medication intake, mental comorbidities, geographical origin, and leisure time in contact with nature. Participants will fill out this data before starting the intervention. Then, preliminary efficacy outcomes will be estimated by psycho-physiological coherence (HRV parameters), blood pressure, and self-perceived quality of life measures.

#### 3.1.1. Blood Pressure

The instruments used to measure blood pressure will be three automatic upper-arm blood pressure monitors, using the same brand and functioning conditions. This device will always be placed on the left arm in a seated resting position and in order to detect any errors or abnormalities, the nurse researchers involved in this project will check out the results.

#### 3.1.2. Psychophysiological Coherence

The primary measure used to assess physiological or personal coherence is the heart rate variability (HRV) [32]. This parameter refers to the changes in the time interval between two consecutive heartbeats [38]. A coherent heart rhythm is defined as a relatively harmonic (sine wave-like) signal with a very narrow, high-amplitude peak in the low-frequency region (typically around 0.1 Hz) of the power spectrum with no major peaks in the other bands [39]. It is characterized by a heart rhythm pattern of elevated amplitude in low-frequency HRV. This coherence signal pattern is identified by a smooth, sinusoidal curve form in the heart rhythms [39]. While too much variability in heart rate can be harmful to efficient physiological functioning, too little variability correlates with a reduced capacity to adapt to environmental demands and stressors [38]. To estimate heart coherence, three parameters of the HRV are used widely:Time-domain [40]: to estimate the amount of variability in time intervals between successive interbeat (the standard deviation of all normal NN intervals (SDNN) and the root-mean-square analysis of successive interval differences (RMSSD);Frequency-domain: to estimate the distribution of the absolute or relative power (energy) into four frequency bands. High-frequency (HF) bands (0.15 to 0.4 Hz) are mainly affected by respiratory rhythms from 9 to 24 breaths per min (bpm) and reflect the parasympathetic activity. Low-frequency (LF) bands (0.04 to 0.15 Hz) are affected by baroreceptor activity and by respiratory rhythms from ~3 to 9 bpm; they reflect both sympathetic and parasympathetic activities. Very low-frequency (VLF) and ultra-low-frequency (ULF) (VLF, 0.0033 to 0.04 Hz; ULF, ≤0.0033 Hz) bands are spectral components with very low oscillations.Non-linear measures: to quantify the non-linear relationship between RR intervals (see [38] for more details).

The instrument to measure HRV parameters will be emWave^®^ Pro Plus device and software (5 min of registering). The emWave^®^ Pro Plus is a scientifically validated heart-rate monitoring system developed by the HeartMath Institute (Quantum Intech, Inc.) that facilitates HRV assessment. This device is very simple to use and completely harmless. It operates throughout a capillary sensor placed on the earlobe that registers heart pulse and rhythms information while users rest seated on a chair and breathe normally, in silence, for 5 min. When the assessment is completed, artifacts on the data can be checked and delated accordingly. It does not require calibration and operates both in Windows and Mac systems.

